| Address any potential problems involving subject identification, recruitment or data collection and how these problems will be resolved. Please refer to section 4.12 of the IRB Guidebook for guidance on describing potential problems in your research.  The inclusion criteria are fairly broad and inclusive. The majority of adults do not meet physical activity recommendations. Therefore, major recruitment problems are not expected. Continuous recruitment will occur for several months until 30 participants have been identified. We believe this period of recruitment is a reasonable expectation.  This study aims to help participants improve their activity using several strategies, including the requirement to self-report pedometer step counts each day. Both groups have been designed to increase physical activity and sufficiently intensive to maintain involvement. Participants will be informed at baseline that daily communication is required and should take less than 5 minutes each day. It is expected that some participants will forget to report their step counts occasionally. To plan for this possibility a pedometer with a 7-day memory display will be provided to participants so that they can still email their steps several days later. When participants forget to report their steps, they will prompted via email to report missing information during their next expected communication. Additionally, since rewards will be provided if a participant meets their daily physical activity goal, it is expected that strengthening of their reporting will also occur. These precautions should limit data collection problems.  One concern is that starting a physical activity program might result in injury. We will be screening potential participants for health problems using the PAR-Q and requiring a physician’s waiver to participate in moderate intensity physical activity intervention for those who indicate a health condition. Both interventions are designed to be equal to or less physically intense than national physical activity recommendations, which limits risk to that which would be experienced usually. We will also be advising stretching exercises to maintain a healthy body and providing stretching handout developed by the American Heart Association and the American Council on Exercise (ACE) (**both included in our application**). |
| --- |

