# Informed Consent Process and Procedures

Informed Consent Process

| You are responsible for ensuring that the approved consent process is followed. In addition, the participant must sign the IRB-approved consent form before any research activity begins. Approval for your study will be withdrawn if informed consent is not obtained and documented properly. Please refer to section 5.0 and the relevant subsections of the IRB Guidebook for guidance on obtaining informed consent.  a. Describe procedures used to present the study to potential subjects to enhance his/her comprehension of the study information and ability to make a choice or to make an informed decision to participate. Include consideration of the language used to ensure that the information is presented using terms that are clear and understandable and that the setting and timing for explaining the research is conducive to good decision-making. Since informed consent is an ongoing process, include procedures used to inform all research subjects of any new information that might affect their willingness to continue participating in the research. If this study involves a longitudinal design, describe a mechanism whereby consent can be renegotiated, as needed, and subjects can be reminded periodically of the terms of their participation in the research.  b. If minors (children under the age of 18) will be recruited for this study, describe the process used to obtain parental consent as well as assent from the minor child. Please refer to sections 5.6 and 5.7 of the IRB Guidebook for guidance on obtaining parental consent and child assent.   c. If persons who are cognitively impaired will be recruited for this study, describe additional procedures used during the consent process to ensure that the prospective subject understands the information presented about the study. Please refer to section 5.14.2 of the IRB Guidebook for guidance on obtaining consent from cognitively impaired individuals.  The consent form has been submitted with this application for review. Minors and persons with cognitive impairments will not be recruited. Recruitment materials and informed consent documents were written in language at the 6th to 8th grade level. At the baseline office visit, before baseline measures are taken, [name] or a research assistant will describe the study again, review the study components, and discuss the time commitments and any risks and benefits. Participants will also be informed of their right to refuse to participate at any time. We will solicit and answer any participant questions at this time. Participants will be required to sign and date the consent form indicating that they have given their consent. Participants will be provided copies of the consent form. If new information about the interventions is learned over the course of the study that changes the benefit to harm balance, or confidentiality, participants will be informed of the changes and reminded of their right to refuse to participate. A phone number will be provided on the consent form, so participants can have future questions answered by project staff. |

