# Research Design and Methods

Description of Research Design

| Describe the research design, the scientific rationale underlying the proposed research and the statistical basis for the structure of the investigation. Specify aims of the research that include the hypotheses to be tested, questions to answer, data to be gathered and tested. Describe procedures used to test the hypotheses. Provide enough information about the research design to allow the IRB to make an informed judgment that the design will allow you to answer your questions and produce valid results. This information is critical to the IRB in weighing the potential benefits of the study as compared to the potential risks. Please refer to section 4.13 in the IRB Guidebook for information on IRB review of research design.  *Research Design.*  This study aims to test an adaptive goal setting intervention with frequent reinforcement (ActiveRewards intervention) to increase the number of steps/day to recommended guidelines for inactive adults by comparing to a fixed goal setting physical activity intervention. The study will be conducted with 30 participants using a two-group randomized controlled trial design with repeated pedometer measures over 6 months. The each group will experience two phases during the study consisting of a no-intervention baseline phase and one of two intervention phases. 31  *Baseline Phase.* Participants in both groups will be asked to wear a sealed Omron HJ-720ITC pedometer for the first 10 days of the study to collect baseline measures of physical activity. The pedometer will be masked with tape to obscure the number of steps taken. This will be done to reduce participant reactions to the pedometer, which will allow for a shorter baseline phase. Participants will remove the tape seal and report their steps via email after 10 days. After completing the baseline phase, participants will be randomized into either the ActiveReward or Comparison intervention groups.  The intervention components for both groups are shown in the table below. Both groups will receive similar components: 1) a pedometer, 2) self-monitoring of physical activity, 3) brief educational materials, 4) motivational prompts, 5) physical activity goals, and 6) voucher incentives.    *•• Pedometer Assessment.* Participants in both groups will be provided an Omron (HJ-720ITC) pedometer on the first day of the baseline phase, and will continue to use the pedometer throughout the entire study. The HJ-720ITC is small 1 7/8''(w) × 2 7/8''(h) × 5/8''(d) lightweight (less than 1.5 ounces) device and can be worn on a participants’ waistband or belt or kept in their pocket. The device is accurate within 3% of actual steps taken.32  *•• Self Monitoring.* Participants will use the pedometer to record the number of steps they accumulate each day. ActiveReward participants will self-report their accumulated steps to the intervention staff each day via email. It is expected to take less than 5 minutes to write an email to report each day. Comparison Group participants will report their steps weekly via email; this should take less than 20 minutes each week. We plan to make reporting easier by requiring participants to report only their ID number, the date, and steps taken. This should limit response burden.  *•• Physical Activity Education Component.* On the first intervention day, participants in both groups will be sent via email two brochures on physical activity. One was entitled, “Be Active Your Way: A Guide for Adults” published by the U.S. Health and Human Services and available at the Centers for Disease Control and Prevention website (www.cdc.gov) (Department of Health and Human Services, 2008). The publication defines physical activity and covers the national recommendations for adults. It also included a number of sections tailored to individuals’ current activity status. These sections included, “Getting Started with Physical Activity”, “Making Physical Activity Part of Your Life”, “Keeping It Up, Stepping It Up” and “Being Active for Life”. The second brochure was entitled, “100 Ways to Add 2000 Steps” by the America on the Move Foundation (www.americaonthemove.org) (America On the Move, 2008). This brochure suggests 100 ways to increase steps throughout the day with the caveat that following only one tip would not provide 2000 additional steps. Tips included “Take your dog for a walk”, “Take an aerobics step class”, “Walk around the outside aisle of the grocery store before shopping”, etc. America on the Move provides these materials free of charge to health professionals and researchers. No further educational materials will be provided to participants. Reviewing these materials is expected to take about 1 hour. The brochures are included with this IRB application.  *•• Motivational prompts.* Participants will receive motivational prompts about their physical activity to help encourage change. It is estimated that one message will be delivered every 2 weeks and participants can chose to receive these via email or text message. The prompts will include motivational messages, reminders about the health risks and benefits of physical activity, and encouraging advice developed by the PIs or research assistants. These prompts may overlap with the messages communicated in the educational component or prompt individuals to re-review the educational brochures. Both groups will receive the same prompts. Reviewing prompt messages is expected to take less than 1 minute each occurrence.  *•• Physical Activity Goals.* Both groups will receive physical activity goals, but groups will differ on the types of goal. The Comparison group will be instructed to try to meet the standard ‘usual care’ goal of at least 10,000 steps each day on at least 5 days per week. This represents a constant and fixed goal to attempt to achieve. As noted in the background selection, this goal approximates the national physical activity recommendation when activities from daily living are included in the count. This goal is commonly heard in the media and has been adopted by physical activity advocacy groups (e.g. America on the Move Foundation). Participants will receive this goal on the first intervention day and will be reminded of it periodically.  ActiveRewards group participants will be prescribed personalized, adaptive goals based on a 10-day moving sample window of their past physical activity measured by the pedometer. Participants will be informed that the goals adapt to their performance. Once a participant emails their pedometer steps, the research staff will send the next day’s step goal via email. Since the goals will adjust daily, each step goal will only good for that day. The percentile algorithm will determine new steps goals.  *•• ActiveRewards Goal Setting Algorithm.* Prior studies using pedometers and goal setting have prescribed goals for participants to meet by adding some progressive amount to participants’ baseline level or have provided a fixed goal, such as 10,000 steps per day, based on guidelines associated with national physical activity recommendations. To our knowledge, no studies to date have applied a continuously adaptive goal-setting algorithm based on participant’s own behavior.  The concept we plan to test is based on percentiles. The Percentiles algorithm requires: 1) continuous and repeated assessments of behavior, 2) rank that sample of behavior from lowest to highest, and 3) apply percentile to that distribution to determine the goal. For example, for one participant, the step count each day for the last 10 days (ranked from lowest to highest) was 1000, 1500, 2600, 4500, 5000, 5700, 6300, 6500, 8000, 11,000. This identifies the distribution of step counts. We plan to use a 70th percentile criterion with a moving 10-day window. Based on this distribution, a goal of 6,300 steps (70th percentile of the distribution) would be provided for the 11th day. Meeting or exceeding this goal would earn a reward voucher for that day. Each new day’s step count will be used to replace the oldest observation of the 10 days, re-rank the distribution, provide a new goal, and slowly but progressively increase participant’s activity behavior over time by always rewarding the top 30% of the distribution of behavior. The algorithm is adaptive, meaning that as physical activity behavior vacillates uniquely for each individual, the algorithm increases or decreases the absolute number of steps so that the goal always represents the best 30% of the last 10 days. Participants will be provided a new goal each day during the intervention phase of the study. **It is important to highlight that prescribed goals will always fall within each participant’s abilities based on a known sample of their behavior from the last 10 days. This is unlike the usual care goal of at least 10,000 steps 5 days per week, which is likely beyond their current abilities.**  One feasibility study to date tested a percentile algorithm for physical activity.33 [name] used a 40th percentile and found a 17% increase in steps/day and 32% increase in their moderate-to-vigorous physical activity minutes/day over baseline. At present, we do not know the specific percentile that will produce optimal change for physical activity behavior. Higher percentiles (e.g. 90th percentile) risk the possibility that a participant may never meet the goal since only best 10% of a participant’s behavior would meet it. As found by contingency management studies aimed at decreasing substance use, this could lead to participants experiencing frustration at the difficulty of the behavior change goals, and lead participants to drop out of the study early.34 A 5th percentile would be too easy and while this would produce consistent physical activity at some level, it would not result in longer bouts of physical activity.  *** Reward Vouchers.* ActiveReward Group participants will earn one reward point each day they reach their step goal over the 6 months. This incentive system is similar to “credit card membership reward points” that can be exchanged for various items and services. Each point will be worth $1.00. It is expected that participants will meet the programmed average of 30% of goals over the course of the intervention. This equals between $52 and $69 (+10% to be conservative) in incentives over the course of the intervention phase. Participants can bank their vouchers to save for larger payouts (e.g., $10 voucher). Participants will not earn or lose vouchers for missing a daily goal or failing to report step counts. Banked vouchers will never be subtracted. Vouchers will be sent electronically in the form of gift cards that can be exchanged after accumulating a minimum of $5 ($5 is the minimum size gift card at many companies). Electronic vouchers will be sent immediately and will be available for a select number of retailers (e.g. Apple iTunes, Amazon.com) or donation websites (e.g American Red Cross, Kiva.org). Participants in prior studies have requested an option for donation websites.  The Comparison Group will receive $70 in incentives during the intervention phase, but instead of earning for accomplishing physical activity goals, they will receive a progressively increasing amount for exchanging their pedometer each month (pedometers need to be exchanged because they only have 40 days of internal memory). Comparison group participants will a total of $70 on the following schedule: $5 for month 1, $10 for month 2, $10 for month 3, $20 for month 4, $25 for month 5. Both Groups will receive $20 for completing the 6-month questionnaire and returning the pedometer.  Finkelstein et al. found that participants who earned $7.00 for every 1% decrease in body fat lost an average 1.5% of their body weight (or 3 pounds for their 200 pound average participant) by the first opportunity earn the reward at 3 months (Finkelstein et al., 2007). In comparison, the current study offers $1.00 for each instance that participants meet their daily personalized goal which was usually less than 10,000 steps. As noted earlier, 10,000 steps/day is equivalent to 5 miles of walking. A 200 pound individual walking five miles at a moderate intensity (i.e. MET = 3.0) would take about 100 minutes and expend about 455 calories, and would earn $1.00. After matching on calorie expenditure, the current study offers an incentive about 119% more (Finkelstein et al.: 10,500 kcal = $10.50; current study: 10,500 kcal =$23.00) for the same calories expended (assuming a fixed caloric intake). However, the current study will not usually prescribe goals this difficult, so this difference could be greater. Nevertheless, compared to Finkelstein et al., the current study maximizes the fidelity of incentives by: 1) providing opportunities to earn smaller rewards more frequently (i.e. a $1 reward each day versus $7 every 3 months), 2) using a direct contingency of reinforcement for physical activity - instead of weight loss, which can include a number of desired and undesired behaviors, and 3) has a shorter latency between the occurrence of physical activity bouts and the presentation of the reward (i.e. the same day versus 3 months later for the Finkelstein et al. study).  **Statistical Considerations**  Our null hypothesis is that the ActiveRewards Intervention group will not differ in their average steps/day change compared to the Comparison intervention over the course of 6 months. The alternative hypothesis is that ActiveReward participants will show greater improvements in their physical activity change compared to the Comparison Group. Specifically, a mean difference of 1,000 steps/day between groups will be considered practically important. This effect is lower than the mean change observed by a recent systematic review of pedometer interventions but realistic given the pilot nature of the current study .26 Because this is a pilot test designed to test the feasibility of using percentiles for promoting exercise, we plan to recruit 30 participants into the study. Thirty individuals is estimated to be sufficient sample to test the concepts and determined to be financial feasible. The pilot study will test the intervention efficacy (i.e., ‘proof of concept’) and will be a preliminary study for future grants to explore this line of research.  **Data Analysis**  **Aim #1.** **To determine whether physical activity (pedometer-measured steps/day) in both the ActiveRewards and Comparison groups increased compared to their respective baseline levels.** We plan to analyze this aim using descriptive and visual methods. Means, standard deviations, and other descriptive data will be summarized by group and intervention phase. Pedometer data will be plotted on a time-series graph and phases delineated to evaluate the change in level, slope, and variability between the baseline and intervention phases of the study for all 30 participants independently and their group means. Regression models may be used to explore change by phase for each group. It is expected that each intervention phase will produce changes in the average number of steps taken per day.    **Aim #2. To evaluate whether the ActiveRewards intervention results in greater change in physical activity (steps/day) relative to the Comparison group.** Since there will be 6 months of daily pedometer data, a multi-level random-effects regression analysis will allow us to detect differences between intervention groups. The independence of observations assumption of many statistical tests are violated with time series data because repeated measures of behavior tend show serial dependence.35The multi-level random-effects analysis will allow us to use all of the available time-unstructured data from the sample of participants without imputing missing values, thus allowing for a smaller sample size. This modeling approach will also allow us to explore the autocorrelation that exists with repeated measures data.36 As noted earlier, a difference of 1000 steps/day between groups would be considered a practically important outcome. |

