| --- |
| Guidance information is available in the [IRB guidebook](http://gra.sdsu.edu/irb). See the following section(s): [4.13](https://sunspot.sdsu.edu/irb/guidance.jsp?anchor=_Toc65256696) |

Subject Involvement

| Describe the tasks the subject will be asked to complete and indicate the amount of time that the subject will be involved in each aspect of the study. Please refer to section 4.13.1 in the IRB Guidebook for information on IRB review of tasks associated with participation. Include a description of any investigational, experimental, or special procedures that involve the study participant (medical devices, electrical equipment, etc.).  The telephone screening will require about 20-30 minutes to complete.  For participants, only one office visit will be required, which will occur at baseline. The remaining intervention components and measurements will be delivered via email or mail. The baseline assessments are expected to take no longer than 1 ½ hours. During the baseline visit participants will fill out the PAR-Q, will have their height and weight measured, answer surveys about their physical activity (IPAQ), neighborhood (NEWS), media use, and learn to use the pedometer.  A 6-month follow-up evaluation on the intervention modality will be conducted by phone and will take approximately 30 minutes.  Participants will be required to report their steps weekly for the Comparison group and daily for the ActiveRewards Group. This will require about 20 minutes weekly or 5 minutes daily.  Reviewing the education materials should take about 1 hour. Reviewing the motivational prompts should take about 1 minute each instance.  This study will require participants to mail their pedometer back to us each month (6 times total). Participants will be provided postage paid envelopes. This will take approximately 30 minutes each instance. |
| --- |
| Guidance information is available in the [IRB guidebook](http://gra.sdsu.edu/irb). See the following section(s): [4.13.1](https://sunspot.sdsu.edu/irb/guidance.jsp?anchor=_Toc65256697) |

Research Instruments

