• Satisfaction with Intervention Modality. At the 6 month intervention, participants will be asked to rate how motivating or burdensome specific study components were to them, and their overall satisfaction with the study. Participants will also asked about their personal experience with the intervention, any side effects or injuries, and their recommendations for improvement. This consumer satisfaction may be helpful for understanding how participants experienced the study, and for improving the intervention (Winett, Moore, & Anderson, 1991).

• Demographic and Socioeconomic (SES) Variables. Demographic variables including sex, ethnicity/race, age, highest educational achievement and household income, will be collected from participants during the phone screening.

• Neighborhood type.Urban form and neighborhood characteristics will be measured using the Neighborhood Environment Walkability Scale (NEWS). The survey includes eight sections measuring self-reported neighborhood residential density, proximity to nonresidential land uses, access to services, street connectivity, walking and cycling facilities, aesthetics, traffic safety, and crime safety. The NEWS has shown good to excellent test-retest reliability and is able to accurately discriminate high and low walkable communities.38-40

• Self-reported physical activity. The International Physical Activity Questionnaire (IPAQ) short form will be used to measure physical activity at baseline to determine whether participants perform less than national MVPA recommendations. The IPAQ asks participants to report their frequency and duration of light, moderate, vigorous, walking, and sitting activities over the last 7 days. The IPAQ has shown to be a reliable and valid measure of physical activity with adult populations.19

Study Location

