# Risk Assessment and Management

| 1. Description of Risks. Describe the potential or known risks associated with participation in this research. Consider and assess the physical, psychological, social, economic and/or legal harm that may result from participation in this study. Discuss whether risks would exceed those likely to be encountered by the individual in their everyday life. Assess whether the risks and inconveniences associated with the research are reasonable in relation to the anticipated benefits to the subjects and in relation to the knowledge that may reasonably be expected to result from this research.  b. Management of Risks. Describe precautions, safeguards and alternatives incorporated into the research activity to reduce or limit the severity, duration and likelihood of harm. If the study activities place the subject at greater than minimal risk for injury, describe what the potential subject will be told during the consent process and describe whether and who will cover treatment for any injury associated with the study.   c. Data Safety Monitoring Board (DSMB). When applicable, discuss the process used to monitor data collected to ensure the safety of subjects (e.g., clinical trial studies). All Phase III randomized clinical trials supported or performed by NCI require monitoring by a DSMB. For more information on DSMBs, please visit the [NCI website](http://deainfo.nci.nih.gov/grantspolicies/datasafety.htm). If this requirement does not pertain to your study, please state 'DSMB - not applicable' in the text box below. Refer to section 4.15.1 of the IRB Guidebook for guidance related to Data and Safety Monitoring Boards.   All research introduces some risk to participants. We believe that the potential risks of this study are minimal to moderate and may be psychological or physical. Participants may experience: 1) anxiety or embarrassment related to one’s personal behaviors related to physical activity habits, answering questions about one’s health or to the measurement process; 2) feelings of inadequacy or embarrassment if unable to succeed at agreed upon activity goals; 3) concern for privacy related to divulging personal information or loss of confidentiality if a computer is accessed by an unauthorized person; 4) physical injuries such as strains or sprains. Judging from our past experience and the current literature, these risks are of relatively low likelihood.   1. Risks of embarrassment or social discomfort will be minimized by fully informing participants of the topics to be discussed and the specific involvement required of them before they agree to participate. Participants will be informed that they may discontinue their involvement at any time, with no impact to the incentives previously received. Staff will be trained to provide a very positive and supportive context for the intervention and assessment. 2. The percentile intervention is designed to specifically to help participants make small, feasible changes in their activity, by prescribing goals that always fall within their previous 10 day sample of activity. These goals can both increase and decrease depending on their activity over the last 10 days. Thus, success at meeting the goals is likely for at least 30% of their attempts. 3. Participants will be told that all responses are confidential. Risks to confidentiality will be minimized by keeping screening forms, informed consent statements and participant data in separate locked file cabinets so that individuals are not easily connected to the study results. When necessary, data will be transferred from prepared forms to electronic files. Participants’ data will be stored on a password-protected computer and identifying information will not be included in the data set. Participants will be told that the SDSU Institutional Review Board will have access to research records. For individuals who do not qualify, their contact information will be destroyed 1 year after participants have been recruited into the study. All participants contact information will be destroyed 1 year after the intervention is completed. We will not re-use or disclose collected health information for other purposes. 4. Encouraging participants to be more physical active by prescribing goals might result in as strains or sprains. It should be noted that the goals participants will be provided will be equal to or less than national recommendations. ActiveReward goals are designed to both increase and decrease based on a moving assessment of their activity using the last 10 days as a window of observation. Physical activity goals for these participants will always be within the observed range of their behavior over the last 10 days. This procedure guarantees that participants will never be provided a goal outside of their abilities.   To minimize the general risk from adopting a more physical active lifestyle, we will screen for health problems with **the Physical Activity Readiness Questionnaire (PAR-Q)** during the baseline assessment. The PAR-Q has been designed to identify the adults for whom physical activity might be inappropriate or those who should have medical advice before starting an activity program. A copy of the PAR-Q has been included in this application. Additionally, we will provide all participants with **the American College of Sports Medicine and American Heart Association tip sheets** on how to minimize risk of injury while being physically active. Examples of the tip sheets have been included in this application. [name] or a research assistant will administer the PAR-Q and review these preventive tip-sheet practices with participants. All activity that participants adopt will be in their free-living environment. No activity will occur at the measurement offices. |

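### Harms are solicited only once, by a retrospective item in the 6-month satisfaction evaluation, and no harms question during the study or at withdrawal is described

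*Protocol*

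**What the plan says.** **Where harms are asked about.** Under Research Instruments, the item on satisfaction with the intervention modality, given at 6 months, includes: "Participants will also asked about their personal experience with the intervention, any side effects or injuries, and their recommendations for improvement". Subject Involvement gives the mode and timing: "A 6-month follow-up evaluation on the intervention modality will be conducted by phone and will take approximately 30 minutes". I found no other place in the protocol where participants are to be asked about injury or side effects.

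**Other contacts.** Subject Involvement states: "For participants, only one office visit will be required, which will occur at baseline". Description of Research Design has ActiveRewards participants email their steps daily and Comparison participants weekly, and keeps these reports short by "requiring participants to report only their ID number, the date, and steps taken". Pedometers are mailed back monthly, six times in all, in postage-paid envelopes. Under Potential Problems, a participant who misses a report is prompted by email for the missing information.

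**Anticipated harms.** Risk Assessment and Management lists feelings of inadequacy or embarrassment over unmet goals, and says of physical injury: "Encouraging participants to be more physical active by prescribing goals might result in as strains or sprains". The measures given are preventive or supportive: the PAR-Q, tip sheets, the design of the goals and staff manner. The form asks there for a monitoring process or a statement that none applies, and the answer gives neither.

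**The commitment to participants.** Informed Consent Process promises to tell them of changes "If new information about the interventions is learned over the course of the study that changes the benefit to harm balance, or confidentiality". It adds: "A phone number will be provided on the consent form, so participants can have future questions answered by project staff".

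**The concern.** How and when harms are collected is fixed in the protocol, and here it is fixed at one point after the participant's exposure has ended. Three things follow.

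- **Recall.** A minor strain or a discouraging spell early in the intervention is first asked about months later.
- **Leavers.** Participants may stop at any time and no harms question at that point is described. Someone who leaves because of an injury might never be asked.
- **The consent commitment.** Nothing planned within the study feeds the promise to pass on new benefit-harm information.

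Unsolicited reports would not fill the gap evenly. One arm writes to staff every day and the other once a week, so the chance of mentioning a problem differs by arm. The protocol itself argues that the fixed 10,000-step goal is likely beyond participants' current abilities while adaptive goals stay within them. On that reasoning, strain or distress could differ between arms.

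The pilot is meant to support future grant applications. A harms account resting on long recall, and possibly without those who left, could make the programme look better tolerated than it was.

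**Working it through.** The protocol states no injury rate, dropout rate or safety figure, so there is none to reproduce. The check sets its own schedule figures side by side.

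**Inputs from the protocol**
- Intervention length: 173 days (Compensation and Incentives, where 0.40 × 173 = 69.2, printed as $69)
- Baseline: 10 days; sample size: 30 (Description of Research Design)
- Reporting: daily in ActiveRewards, weekly in Comparison
- Pedometer mailings: monthly, six in total, both arms (Subject Involvement)

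**1. Recall window.** The study lasts 10 + 173 = 183 days. An injury on the first intervention day is first asked about roughly 173 days later. An item at each of six mailings would cut the longest window to about 173 / 6 ≈ 29 days.

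**2. Routine contacts by arm.** ActiveRewards has 173 daily emails. Comparison has 173 / 7 = 24.7, about 25. The ratio is 7 to 1. This counts opportunities to volunteer something, not reports: the emails ask for no harm information in either arm.

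**3. When the first solicited answers arrive.** Recruitment is described only as: "Continuous recruitment will occur for several months until 30 participants have been identified". Let it last R months (an assumption).
- The first enrollee is called at month 6. If R is 6 or less, nobody has been asked about injury before the last participant enrols.
- At that call the last enrollee has been in the study 6 − R months and so has 6 − (6 − R) = R months left. With R = 4, that is 4 months.

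Early answers therefore come too late for enrolment decisions, but while later enrollees are still exposed.

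**4. Effect of missing injured leavers (illustration only).** Let p be the proportion injured and m the share of the injured who leave and are not reached. Both are assumed. Expected count = 30 × p × (1 − m), and P(at least one counted) = 1 − (1 − p(1 − m))^30.

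| p | Expected, m = 0 | P(≥1), m = 0 | Expected, m = 0.5 | P(≥1), m = 0.5 |
|---|---|---|---|---|
| 5% | 1.5 | 0.785 | 0.75 | 0.532 |
| 10% | 3 | 0.958 | 1.5 | 0.785 |
| 20% | 6 | 0.999 | 3 | 0.958 |

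At a 5% injury rate, missing half of the injured takes the chance of recording even one case from about four in five to about one in two.

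**The case against.** The other side has several good points.

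- **The commitment is conditional.** It applies if something is learned. That can come from spontaneous emails, a call to the number on the consent form, or outside evidence. A reader might infer that the promise cannot be kept. The protocol does not support that; it shows only that no planned in-study data source stands behind it.
- **Leavers are not excluded from the call.** A reader might infer that injured dropouts go uncounted. No section restricts the 6-month evaluation to completers, and the $20 payment encourages response. Missing them is a risk, not a stated feature.
- **Calls are staggered.** A reader might infer that an excess of injuries would emerge only after all exposure is over. That holds for each participant but not for the trial, as step 3 shows.
- **No safety aim is stated.** The three aims are change in steps, the between-group difference in steps, and satisfaction. No planned comparison is invalidated. The risks are rated of relatively low likelihood, and preventive screening is specified.
- **Thirty people cannot bound injury rates tightly, however often they are asked.** With no injuries in 30, the one-sided 95% upper bound is 1 − 0.05^(1/30) = 9.5%.
- **Unseen material.** The consent form and attached instruments may tell participants to report injuries.

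All of this limits the size of the point. None of it supplies a second solicited harms question, shortens the recall window or makes volunteered reports comparable between arms. The risk rating does not settle matters either: Risk Assessment and Management says minimal to moderate, while Costs says the study does not exceed minimal risk.

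**Conclusion.** The point holds as a cheap improvement. On the text at hand, the only solicited harms question is one retrospective item at 6 months, with recall of up to about 173 days. No harms question is described between baseline and that call, or at withdrawal. Injuries or goal-related distress may be recalled poorly or missed in people who leave. The commitment to pass on benefit-harm information has no planned in-study data source. Volunteered reports, with about seven times as many routine contacts in one arm, would not be comparable between arms.

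The recall window and contact counts follow from the protocol's own figures. The recruitment length, injury rates and share of injured people missed are assumptions. The steps/day analysis is not affected. The main uncertainty is whether the consent form or attached instruments contain a reporting instruction. Such an instruction would help with spontaneous reports but would not by itself be a scheduled question put equally to both arms.

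**What to change.** 1. Put one short item, identically worded in both arms, at each monthly pedometer exchange: any injury, side effect or distress about goals since the last exchange, whether activity was limited, and whether care was sought. Subject Involvement mentions only the pedometer and an envelope, so this needs a slip added to the mailing or an email sent with it.
2. Ask the same item once of anyone who withdraws or stops reporting. The existing email prompt for missed reports can carry it in the latter case.
3. Have an existing study role review the answers from both arms as they arrive, so that the consent commitment has a data source.
4. Keep the 6-month question as the last reporting window.
5. Report solicited injuries by arm descriptively, and list spontaneous reports separately.

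**Cost:** about a minute per month per participant, a short new item needing an IRB amendment, some staff time for review, and a slight reminder effect that is equal in both arms. If the consent form or instruments already give a reporting instruction, refer to it in the protocol and align the item with it.
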